#### Baseline measures

Demographic detail and health information will be collected. Cognitive function will be assessed with the Mini Mental State Examination [29]. The number of previous falls and fractures will be recorded.

#### Primary outcomes

1. Frailty will be measured using the definition of the frailty syndrome by Fried and colleagues [16]. The tool measures five components of the frailty syndrome. One point is scored for each criterion met to specification, with participants meeting 3, 4 or 5 criteria defined as frail. To assess the effects of the intervention program, we will calculate an index score based on the five components. The components are:

a) Unintentional weight loss. At baseline the participant will be asked whether they have lost more than 4.5 kg unintentionally in the past year and their weight will be measured with scales. This criterion is positive if there is unintentional weight loss of more than 4.5 kg, or greater than 5% of body weight in the previous year.

b) Self-reported exhaustion. The participant will be read two statements from the Center for Epidemiologic Studies-Depression Scale [30]:

• "I felt that everything I did was an effort"

• "I could not get going"

The participant will then be asked how often in the last week he/she felt this way. 0 = rarely or none of the time, 1 = some or a little of the time (1–2 days), 2 = a moderate amount of the time (3–4 days), 3 = most of the time. A score of 2 or 3 is a positive response.

c) Weakness. Grip strength will be measured using a dynamometer (Saehan Dynamometer, model SH5001). The best of three attempts will be used. Using a simplification of the cut-off value for grip strength used by Fried et al [16], male participants who score 30 kg or less will be classified as having weak grip strength. Female participants with a score of 18 kg or less will be classified as having weak grip strength.

d) Slow walking speed. The time to walk four metres will be measured, with or without a walking aid. Those participants with a walking time of six seconds or more will be classified as having slow walking speed. The values used by Fried et al [16] have been modified slightly for ease of assessment. Cesari and colleagues [31] determined that older persons with a usual walking speed of one metre per second or less is indicative of poor health outcomes.

e) Low physical activity level. Participants will meet the criterion for physical inactivity if, in the past three months, they did not perform weight-bearing physical activity, spent more than four hours per day sitting, and went for a short walk once per month or less. This is a modification of the definition used by Cesari and colleagues [32].

2. Mobility will be assessed using the lower extremity continuous summary performance score [26] with data collected according to the methods described in the Short Physical Performance Battery [33]. The ability to stand (for 10 sec) with the feet together in the side-by-side, semi-tandem, and tandem positions, time to walk 4 metres, and time to rise from a chair and return to the seated position 5 times is examined. Performance for each component will be recoded as a score between 0 and 1 and summed using the methodology developed by Onder et al [26].

#### Secondary outcomes

1. Hospitalisations and admissions to nursing care facilities will be reported on the monthly calendars then confirmed from general practitioner or hospital records, or the appropriate facility.

2. Activities of daily living status will be measured by the Barthel Index [34], using the 100 point version.

3. The EQ-5D (EuroQol) will measure health related quality of life and provide utility weights to enable evaluation of cost-effectiveness [35]. The EQ-5D contains a visual analogue scale (0 to 100, representing dead to excellent health state) and five items: mobility; self-care; usual activities; pain/discomfort; and anxiety/depression.

4. Psychological status will be assessed using the Geriatric Depression Scale (short form) [36].

5. Falls risk assessment will be conducted with the Physiological Profile Assessment. This tool has been validated and includes five valid and reliable measures of physiological functioning – visual contrast sensitivity, lower limb proprioception, quadriceps strength, reaction time and postural sway. In multivariate models, weighted contributions from these five variables provide a falls risk score that can predict older people at risk of falling with 75% accuracy in both community and residential care (hostel) settings [37].

6. Additional measures of balance and mobility include the Step Test [38], co-ordinated stability test [39], Activity Measure for Post Acute Care [40] and Nottingham Extended Activities of Daily Living Index [41].

7. Participation, the individual's role in a life situation, will be measured via the Reintegration into Normal Living Index [42], Goal Attainment Scale [43], Life Space Assessment [44] and the question 'Do you get out as much as you would like?' [45].

8. Occurrence of falls will be ascertained via monthly falls calendars [46]. When a fall is recorded, the researcher will determine the time of the fall, location, mechanism and contributory factors, and whether injury has occurred, via telephone.

9. Deaths will also be recorded and verified with reference to hospital or general practitioner records.

10. Health and community service use will be recorded using monthly calendars and will be used in economic analyses.

#### Additional measures

Adherence measurements will record both the ability of health and other services to provide the recommended interventions, and the acceptance of these by the study participant.

### Treatment Allocation

#### Randomisation

Permuted block randomisation is used to achieve balanced treatment allocation [47]. A set of permuted blocks was generated for each of two strata ('frail' with 3 frailty criteria and 'very frail' with 4 or 5 frailty criteria). A random number sequence was generated for the order of treatment allocation within the blocks using the SPSS v15 RV.UNIFORM function. Varying block sizes were used. The blocks were randomly arranged within larger sized blocks. Random group allocation will be managed by project personnel not involved in measurement or intervention. The treatment allocation tables for both strata will be stored centrally off site.

#### Allocation Concealment

Enrolment of participants will be managed by the Research Consultant who will screen for inclusion criteria, seek informed consent and conduct the baseline assessment. Following completion of baseline assessment, the Research Consultant will telephone the central study office; the participant will be assigned a participant number and allocated to the intervention or control group. Staff performing the outcome assessment and data analysis will be blinded to group allocation but it is not possible to blind participants and staff administering interventions to group allocation.

### Intervention

Participants of the intervention group will receive a multidisciplinary, multifactorial intervention for one year following discharge from hospital and community rehabilitation services. The interventions will be tailored to each participant, based on their frailty characteristics assessed at baseline. Case management and weekly case conferences will facilitate coordination of the multidisciplinary delivery of the intervention.

For participants meeting the weight loss criterion, a clinical evaluation of nutritional intake at home will be made. Home delivered meals will be recommended if appropriate clinical criteria apply. In addition, if the participant's body mass index (BMI is weight in kilograms divided by height in metres squared) is < 18.5, or mid upper arm circumference is < the 10^th ^percentile (using Australian age and gender specific norms), nutritional supplementation will be offered using commercially available, high energy, high protein supplements.

If the participant reports exhaustion and the Geriatric Depression Scale score is high, consideration will be given for referral to a psychiatrist or psychologist. Where the participant is socially isolated, options will be identified to encourage greater social engagement, e.g. participation in day activity groups and telephone contact with a volunteer.

Participants classified as having grip weakness, slow four metre walk time, or low physical activity level will receive up to ten home-based physiotherapy sessions and perform a home exercise program, over the course of one year. To assist in intervention prescription, the study physiotherapist will evaluate self-efficacy using the Exercise Self-efficacy scale [48], assess stage of motivational readiness for change using the Physical Activity Stages of Change Questionnaire [49] and appraise the goal identified in the Goal Attainment Scale at baseline assessment. Findings from these assessments will be used to design a targeted, goal-focused, home-based strength, balance and endurance training regimen using the program Weight Bearing Exercise for Better Balance (WEBB) [50]. Appropriate mobility aids and other equipment will be recommended as part of this component of the intervention.

In addition, the participant's general health status will be assessed. Where appropriate, chronic disease management programs will be put in place or reinforced with the assistance of currently available health services. The principles of comprehensive geriatric assessment will be used, with careful follow-up of chronic diseases, pain and other identified conditions such as urinary incontinence. Medications will be reviewed and any apparent sub-optimal medication use will be discussed with the participant's general practitioner. Methods to encourage compliance with medications, including education about the reasons for the medication, will be provided to the participant and measures to encourage compliance with medication regimens (e.g. medication packaging in blister packs and reminder cards) will be initiated or reinforced. When the older person's family carer is noted to be experiencing significant distress due to the carer role, a supportive intervention will be provided to the carer.

Participants in the control group will receive the usual care available to older residents of Hornsby Ku-ring-gai area from their general practitioner and community services.

### Sample Size

It will be necessary to recruit approximately 230 participants, to detect a clinically and statistically significant 15% difference in lower extremity continuous summary performance score between the two groups (power = 80%, p = 0.05, dropouts = 15%, non-compliance = 15%, SD = 0.7) [26]. When 100 subjects have been recruited, means and standard deviations from baseline data will be used to check this calculation and conduct power calculations for the frailty index score.

### Statistical Analysis

The design of the study provides for three assessments with study participants – at entry, at three months, and at twelve months after the start of the intervention. Data will be coded to permit blinding to group allocation in the statistical analysis. Analysis will accord with the 'intention-to-treat' principle [51].

Prior to analysis, composite continuous scores will be created for the Fried frailty scale, using a similar methodology to the lower extremity continuous summary performance score. Between group differences in the primary outcome and secondary measures at the three month and twelve month follow-ups will be analysed using ANCOVA models where baseline values are entered as covariates. Logistic regression models will be used to compare groups on dichotomous outcomes. Non-parametric techniques will also be used where appropriate. Baseline variables will be examined, and if there are important differences between the randomisation groups these differences will be adjusted for in the models.

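### Visit-wise ANCOVA leaves the 3-month score and the randomisation stratum out of the 12-month comparison, which can bias the 12-month difference if loss to follow-up works differently by arm

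*Protocol article*

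**What the plan says.** All references are to the protocol article.

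- **Statistical Analysis.** Participants are assessed at entry, three months and twelve months. Between-group differences at the two follow-ups "will be analysed using ANCOVA models where baseline values are entered as covariates". Other baseline variables enter only if an important imbalance is found. The same section states that "Analysis will accord with the" intention-to-treat principle. Neither follow-up is named as the primary time point.
- **Sample Size.** "It will be necessary to recruit approximately 230 participants", with these inputs: "power = 80%, p = 0.05, dropouts = 15%, non-compliance = 15%, SD = 0.7". Loss of primary outcome data is therefore expected.
- **Randomisation.** "Permuted block randomisation is used to achieve balanced treatment allocation", within two strata: three frailty criteria, and four or five. The stratum is not named in the analysis model.
- **Secondary outcomes.** "Deaths will also be recorded and verified with reference to hospital or general practitioner records". Death is not linked to either primary score.
- **Allocation Concealment.** Outcome assessors and analysts are blinded. Participants and the staff delivering the intervention are not.

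**The concern.** An ANCOVA of the score at one visit needs a score at that visit. Someone seen at entry and three months but not at twelve contributes nothing to the 12-month comparison unless a further step is added, even though the trial holds the measurement most likely to indicate how that person was doing.

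Two features make this more than a technicality here. Participants are at least 70 and meet three or more frailty criteria, and the Background reports that frailty predicts worsening mobility, hospitalisation and death, so loss linked to decline is likely. In addition, only one arm receives a year of case management and home visits, and participants know their arm, so the reasons for leaving could differ between arms. If those who are declining leave mainly from one arm, those who remain in it look better than the arm as randomised.

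The stratum is a smaller matter. Allocation is balanced within strata, so the stratum is unlikely to be picked up by a rule that adjusts only for observed imbalance. Leaving it out tends to make standard errors slightly too large. Baseline frailty as a covariate would recover part of this for the frailty outcome.

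**Working it through.** **1. Expected loss.** From the Sample Size section, 230 × 0.15 = 34.5, so about 35 people would lack a 12-month score and 230 × 0.85 = 195.5 would have one.

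**2. What difference the plan targets.** The target is a "15% difference in lower extremity continuous summary performance score between the two groups", with no reference mean, so 230 can be neither reproduced nor refuted. Working back, the detectable difference is d = SD × (1.96 + 0.84) × √(2/n), with SD 0.7 and n per arm (1:1, two-sided 5% and 80% power; the ratio and sidedness are assumed).

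- Dropout only: n = 195.5/2 = 97.75, d = 0.281, implied mean 0.281/0.15 = 1.87.
- Dropout and non-compliance both as divisors: 230 × 0.85² = 166.2, n = 83.1, d = 0.304, implied mean 2.03.

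True effects of 0.28 and 0.30 are therefore reasonable for illustration. The point under review does not change the figure of 230.

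**3. Bias by reason for loss.** Assumed inputs: SD 0.7; correlations 0.6 (entry and 3 months), 0.5 (entry and 12 months) and 0.7 (3 and 12 months); true differences 0.14 at 3 months and 0.28 at 12 months; 15% missing at 12 months; log-odds of loss rising by 1 per SD of worse score where loss depends on a score. There were 400,000 simulated participants per row. The last column fills in missing 12-month scores from baseline, arm and the 3-month score.

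| Loss at 12 months depends on | Visit-wise ANCOVA | Using 3-month score |
|---|---|---|
| Nothing (random) | 0.281 | 0.281 |
| Baseline | 0.277 | 0.279 |
| Baseline, unequal arm rates (19% v 11%) | 0.279 | 0.279 |
| 3-month score, both arms | 0.275 | 0.280 |
| 3-month score, control arm only | 0.237 | 0.280 |
| Unseen 12-month score, both arms | 0.262 | 0.268 |
| Unseen 12-month score, control arm only | 0.200 | 0.224 |
| Unseen 12-month score, unequal arm rates | 0.227 | 0.243 |

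In the fifth row the shift is 0.280 − 0.237 = 0.043, with 16.8% lost in the control arm and 13.1% in the intervention arm. With no true effect, the same mechanism gives −0.042 by visit-wise ANCOVA and 0.000 when the 3-month score is used. When loss depends on the 3-month score equally in both arms, the null result is unbiased (−0.001).

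**4. At trial size.** 3,000 simulated trials of 230 were run with true effect 0.30, correlations 0.6 to 0.75, about 15% missing, and control loss tied to the 3-month score (odds ratio e per SD).

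- Visit-wise ANCOVA: mean 0.268, standard error 0.080.
- Likelihood analysis also using the 3-month score: mean 0.301, standard error 0.078.
- Shift: 0.300 − 0.268 = 0.032, which is 11% of the effect and 0.032/0.080 = 0.4 of a standard error.

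A repeat gave 0.271 and 0.302, with a bias of about −0.03 when there is no true effect. With the dependence on the 3-month score equal in both arms, the estimate was 0.292 to 0.296 against 0.30, a shift below 0.01.

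**The case against.** **Silence is not exclusion.** The article does not say that unmeasured participants are excluded or that imputation is ruled out. Missing-data rules are commonly left to a full protocol or analysis plan, which is not shown. This stands: their absence is no error, and no claim is made that the trial will drop these people. What remains is the named model, which by itself does not use the 3-month score at twelve months.

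**Intention-to-treat.** A reader might infer that visit-wise ANCOVA contradicts the intention-to-treat statement. The text does not support that. Analysing people in the arm to which they were randomised is compatible with this model. At most, the model does not by itself compare everyone randomised.

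**Bias is not certain.** This also stands. Baseline-adjusted ANCOVA is essentially unbiased when loss is random or depends on baseline and arm, even with 19% v 11% loss. Material bias needs a mechanism that differs by arm or acts through the unseen outcome. The documents make the first plausible but do not establish it.

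**A larger figure is tempting.** If losses were 20% v 10% and those lost scored 1 SD lower, 0.7 × (0.20 − 0.10) = 0.07. That describes an unadjusted difference in means. It carries over to the planned model only if the lost are 1 SD lower after baseline adjustment, for which there is no evidence.

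**The remedy is incomplete.** A repeated-measures model treats scores after death as missing at random, and the last three table rows show only partial correction when loss depends on the unseen score. This is why a sensitivity analysis for death is needed. The life-expectancy criterion and the telephone follow-up of calendars lessen the problem without removing it.

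**Conclusion.** The point holds as a matter of choosing a better model. The stated analysis ignores the 3-month score and the stratum in the 12-month comparison, and about 35 of 230 people are expected to be lost. The resulting bias in the 12-month difference is conditional:

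- about 0.03 on a true 0.30 (0.04 on 0.28 with the other inputs) if loss depends on the 3-month score in one arm only;
- about 0.01 or less if that dependence is the same in both arms;
- zero, within simulation error, if loss is random or depends only on baseline and arm.

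These sizes rest on assumed correlations, effects and loss mechanisms. Only the SD of 0.7, the 15% dropout and the 230 come from the article. In the one-arm scenarios run, the control arm lost its decliners, so the estimate moved towards no effect; the mirror case would move it the other way.

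A reader might also take twelve months to be the primary time point. The article gives both follow-ups equal standing, so the conclusion concerns the 12-month result for the primary outcomes, not a designated primary result. Nor can it be concluded that deaths, or tests a participant cannot perform, are left without a rule: the full plan or the cited scoring method may supply one. The change is worth making before analysis, but the flaw does not invalidate the trial.

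**What to change.** Analyse each primary outcome in one mixed model for repeated measures with the 3- and 12-month scores as outcomes and terms for treatment by visit, baseline by visit and randomisation stratum. Report both the 3- and 12-month contrasts from it. An acceptable alternative is ANCOVA with the stratum added, after multiple imputation carried out by arm and using the 3-month score. The 3-month score should enter as an outcome or an imputation variable, not as a covariate in the 12-month model, because it is itself affected by treatment.

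Add a prespecified sensitivity analysis that ranks death below every observed score, since neither option gives a meaningful score after death. If the full plan already contains such rules, cross-reference them.

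The cost is revised analysis wording, slightly more analysis work and explicit reliance on missing at random. No new data are needed, and the simulation showed no loss of precision (standard error 0.078 against 0.080). People with no follow-up score add nothing to the mixed model, so their number by arm should be reported.

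### Covariates are to be picked from observed baseline imbalance, and the stated models omit the randomisation stratum: the model stays open until data are seen, tests run slightly conservative, and a little power may be lost

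*Protocol article*

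**What the plan says.** **Models.** The Statistical Analysis section says that between-group differences at three and twelve months "will be analysed using ANCOVA models where baseline values are entered as covariates". For binary endpoints, "Logistic regression models will be used to compare groups on dichotomous outcomes", and no covariate is named.

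**Further covariates.** After baseline variables have been examined, "if there are important differences between the randomisation groups these differences will be adjusted for in the models". The section does not list the variables, define what counts as important, or confine the rule to sensitivity analyses, so it covers the primary models.

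**Randomisation.** The Randomisation section says "A set of permuted blocks was generated for each of two strata": 3 frailty criteria, and 4 or 5. It adds "Varying block sizes were used" without giving the sizes. The Statistical Analysis section does not mention the strata.

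**Related text.** Group codes are masked for the analysis. The Baseline measures section records previous falls and fractures.

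**The concern.** Under concealed randomisation, a baseline difference between groups arises by chance. Its size says nothing about whether the variable predicts outcome. A rule triggered by imbalance can therefore adjust for an irrelevant variable that happens to differ and pass over a strong predictor that happens to balance. Because 'important' is a judgement, the primary model is not settled until someone has looked at the data. In logistic models the covariate set also changes which odds ratio is being estimated, so the target of estimation is left open too.

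The stratum is the clearest case. The trial team thought frailty severity worth stratifying on. Stratified blocks keep it balanced, so the rule will pass it by. If severity predicts outcome, a model without it puts the between-stratum variation into the residual, although the design has already removed that variation from the treatment contrast. The standard error is then too large for the design: the test is conservative and some power is lost.

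**Working it through.** **1. The plan's own figure.** The Sample Size section gives about 230 participants for a 15% difference in the mobility score (SD 0.7, power 80%, p = 0.05, dropout 15%, non-compliance 15%). The mean to which the 15% applies is not stated, so 230 can be neither confirmed nor refuted. With an assumed mean of 2.0, the difference is 0.30 and n per arm = 2 × (1.96 + 0.8416)² × 0.49 / 0.09 = 85.5, so 86, or 172 in total. Inflated, that is 172 × 1.15² = 228 or 172 / 0.85² = 239. Nothing below depends on this mean except the simulated powers in step 4, which use an assumed difference of 0.26.

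**2. Would the rule ever select the stratum?** Assume 40% in the 4-or-5 stratum and blocks of at most 6 (neither is in the article). Only an unfinished last block can unbalance a stratum, so the arms differ by at most 3 within it. A worst case is 48 of 115 against 45 of 115: a difference of 0.026, standard error √(0.404 × 0.596 × 2 / 115) = 0.065, z = 0.40. That is far from any usual threshold.

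**3. Effect of omitting the stratum, closed form.** Let R be the model standard error without the stratum divided by that with it. Then true size = 2 × (1 − Φ(1.96R)), and power at an 80% design = Φ(2.80 − 1.96R). The stratum's share of the variance left after baseline is 1 − 1/R².

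| Stratum effect beyond baseline | R | Share of residual variance | True size | Power without stratum |
|---|---|---|---|---|
| None | 1.000 | 0% | 0.050 | 80% |
| Weak | 0.0765/0.0752 = 1.017 | 3.3% | 0.046 | Φ(0.807) = 79% |
| Strong | 0.0808/0.0756 = 1.069 | 12.5% | 0.036 | Φ(0.705) = 76% |

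**4. Simulation of the rule as written.** Inputs from the article: 230 less 15% dropout, so 196 analysed; stratified permuted blocks; 5% test, taken as two-sided. Assumed inputs: baseline coefficient 0.5 to 0.6, eight candidate covariates, p < 0.05 as 'important', blocks of 2, 4 and 6. There were 6,000 runs per scenario (Monte Carlo error about 0.003 for size).

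| Scenario | Size, baseline only | Size, imbalance rule, no stratum | Power, imbalance rule, without vs with stratum (difference 0.26) |
|---|---|---|---|
| No stratum effect | 0.046 | 0.045 | 90.4 vs 90.3% |
| Weak | 0.042 | 0.038 | 93.0 vs 93.5% |
| Strong | 0.035 | 0.032 | 90.5 vs 93.3% |
| Strong, and stronger other covariates | 0.037 | 0.029 | 92.8 vs 94.6% |

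With the stratum and a fixed covariate set, size was 0.047 to 0.054. Two further simulations of the rule at a cut-off of about 1.96 gave sizes of 0.035 to 0.047 and 0.033 to 0.048, which agree within simulation error.

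**5. If the model is chosen on its result.** Taking the smallest p-value over four candidate models gave sizes of 0.052 to 0.058. Taking it over several imbalance cut-offs gave 0.055 to 0.065 in one simulation and 0.056 to 0.073 in another.

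**6. Which outcomes are affected.** The baseline frailty index is built from the same five components that define the stratum, so little remains for the stratum to explain. Only walking speed is shared with the mobility score, so the stratum can add information there. Admissions and death have no baseline value, so their stated models contain no measure of frailty severity.

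**The case against.** **The stratum is missing only by silence.** The article does not say that baseline values are the sole covariates, and an analysis plan that is not shown may add the stratum. That is fair, and the omission alone would be a weak point. The imbalance rule, however, is stated text. A plan that fixed its covariates in advance would have to overrule it.

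**A reader might infer that the rule inflates false positives, even to 8 or 9%.** The documents do not support this. Applied mechanically, the rule errs the other way. A size of 8 to 9% comes from one simulation that took the smallest p-value over five cut-offs, and the repeat simulations in step 5 did not reach it. The article describes no such selection. Masked group codes hide the direction of benefit; they do not fix the model, but neither do they suggest that it will be chosen on its result.

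**A reader might infer a large loss of power.** One simulation gave 81% under the rule against 90% with constant adjustment, for a covariate correlated 0.5 with outcome (80% against 83% at 0.3). Since the outcome's baseline value is already in the model, that correlation would have to be additional to it. No figure in the article supports this.

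**A reader might infer that falls have no baseline counterpart.** Previous falls are recorded at baseline. No stated model uses them by name, but they are available. The lack of any baseline value holds for admissions and death.

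**Conclusion.** The point stands as a modest one about prespecification and efficiency. The article fixes a poor rule for choosing covariates and names no model containing the factor on which it stratified, a factor the rule would almost never bring in. Applied mechanically without the stratum, the rule gives a true size of about 0.03 to 0.047 for a nominal 0.05. Omitting the stratum costs about 0 to 4 points of power: near zero for the frailty index, and potentially more for mobility, admissions and death. Size rises above 5%, to about 5 to 7%, only if the model is picked on its result.

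The direction follows from the design. The sizes rest on assumptions that the article does not supply: the share in each stratum, how far the stratum predicts outcome beyond baseline, the number and strength of other covariates, the threshold for 'important' and the block sizes. If the stratum predicts nothing beyond baseline, including it gains nothing and costs essentially nothing.

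**What to change.** Replace the imbalance sentence with a fixed specification:

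- Every model contains treatment, the outcome's baseline value where one exists (previous falls for falls) and the randomisation stratum (3 versus 4 or 5 criteria).
- Any further covariates are chosen for expected prognostic value and listed before allocation codes are broken.
- Baseline imbalance is reported descriptively. Any adjustment prompted by it is a labelled sensitivity analysis.

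The cost is a change of wording in the analysis section or the statistical analysis plan. The stratum is known at randomisation and the baseline measures are taken before it, so no new data are needed and the target of 230 is unchanged.
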